##### Handling of missing data

For primary outcome data missing due to subject withdrawal or loss to follow-up, multiple imputation (MI) will be performed using 5 independent imputation cycles. Predictors for imputation will include baseline demographic and clinical characteristics (age, gender, BMI, ASA physical status), intraoperative factors (surgery duration, anesthesia duration, total sufentanil dosage), and available partial outcome data. A fixed random seed (12345) will be set to ensure reproducibility of the imputation results.For secondary outcome data with missing values, complete-case analysis will be performed, and the proportion of missing data will be reported.No imputation will be performed for safety data; all reported adverse events will be included in the safety analysis regardless of subject withdrawal status.

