#### Sample size calculation

The sample size calculation is based on the dual co-primary endpoints of this trial: the non-inferiority of analgesic efficacy (PACU pre-rescue NRS pain score) and the superiority of diaphragmatic safety (incidence of hemidiaphragmatic paralysis, HDP). All calculations are performed using PASS 15.0.5 software (NCSS, LLC, Kaysville, UT, USA) with a one-sided significance level (*α*) of 0.025 and a statistical power (1-*β*) of 0.80, consistent with the design of randomized non-inferiority trials in anesthesiology.

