##### Sample size calculation based on analgesic efficacy non-inferiority endpoint

The primary non-inferiority endpoint is the difference in pre-rescue NRS pain scores between the 2 mL group and the 5 mL group immediately after full consciousness in the PACU. The predefined non-inferiority margin is 1 point on the 11-point NRS scale, which is widely accepted as the minimal clinically important difference (MCID) for postoperative pain assessment in orthopedic surgery. This margin was also used in previous similar trials comparing different volumes of local anesthetic for brachial plexus block.

Based on the results of our preliminary study (*n* = 11) and previously published literature, the standard deviation (SD) of NRS pain scores in patients undergoing arthroscopic shoulder surgery with upper trunk brachial plexus block is estimated to be 1.6. Using the two-sample Z-test for non-inferiority with pooled variance, the required sample size per group is calculated as follows:
$$n=\frac{2{\left(Z_{1-\alpha }+Z_{1-\beta }\right)}^{2}\sigma^{2}}{\delta^{2}}$$
Where 
$Z_{1-\alpha }=1.96$
 (one-sided *α* = 0.025), 
$Z_{1-\beta }=0.84$
 (power = 0.80), 
σ=1.6
, and 
δ=1
 (non-inferiority margin). Substituting the values yields a required sample size of 40 patients per group.

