##### Final sample size determination

The larger sample size requirement from the two co-primary endpoints is 40 patients per group. To account for potential subject withdrawal or loss to follow-up during the trial, we will recruit additional subjects to ensure that the final ITT analysis set includes at least 40 patients per group. Considering a conservative dropout rate of 20%, we will recruit a total of 100 patients (50 patients per group) for this trial.

Any subjects who withdraw from the study before completing all primary outcome assessments will be replaced by newly enrolled subjects in strict sequential order to maintain the integrity of the randomization sequence and ensure the required statistical power.

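### Five imputations leave avoidable seed-dependent noise in the bounds that decide both co-primaries; at least 50 would remove most of it at no real cost

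*Protocol article*

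**What the plan says.** Under Handling of missing data, the protocol article covers the co-primaries as follows: "For primary outcome data missing due to subject withdrawal or loss to follow-up", "multiple imputation (MI) will be performed using 5 independent imputation cycles". It adds: "A fixed random seed (12345) will be set to ensure reproducibility of the imputation results". The predictors are to include age, gender, BMI, ASA status, surgery and anesthesia duration, total sufentanil dose and whatever partial outcome data exist.

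Definition of analysis populations makes the ITT set primary for both co-primaries. Analysis of primary outcomes settles each on one bound: the upper one-sided 97.5% bound for NRS must lie below 1, and the lower one-sided 97.5% bound for the HDP risk difference must lie above 0. Multiplicity adjustment requires both to succeed.

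On the amount of loss, Final sample size determination says: "Considering a conservative dropout rate of 20%, we will recruit a total of 100 patients (50 patients per group) for this trial". Sensitivity analyses lists a complete-case re-analysis of the primary outcomes.

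**The concern.** A multiple-imputation result carries its own random error, which shrinks as the number of imputations grows. Fixing the seed settles which random draw is used. It does not bring that draw nearer to the answer that many imputations would give.

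Both success rules compare a bound with a fixed threshold, so this error goes straight into the verdict. With few imputations and appreciable missing data, a trial whose bound lies near the threshold could pass under one seed and fail under another with identical patient data. The article fixes the number at 5. It does not tie that number to the missing fraction and gives no check on Monte Carlo error.

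**Working it through.** **Inputs from the article.** 5 imputations and a fixed seed (Handling of missing data); 50 per arm and 20% dropout (Final sample size determination); SD 1.6 and a margin of 1 point (the NRS sample size section); HDP 16.67% against essentially 0 (the HDP sample size section); one-sided α 0.025 and power 0.80 (Sample size calculation).

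**The plan's own figures first.**
- NRS: 2 × (1.96 + 0.84)² × 1.6² / 1² = 2 × 7.84 × 2.56 = 40.1.
- HDP: 7.84 × (0.1667 × 0.8333) / 0.1667² = 39.2.
- Both agree with the stated 40 per group, and 40 / 0.80 = 50 per arm.

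**NRS by hand, 10 missing per arm, predictors uninformative.**
- Variance of the mean difference with complete data: 2 × 2.56 / 50 = 0.1024.
- With 40 observed per arm: 2 × 2.56 / 40 = 0.128, an SE of 0.36.
- Between-imputation variance: about 0.128 − 0.1024 = 0.0256.
- Between-seed SD of the point estimate: √(0.0256/5) = 0.072 with 5 imputations, √(0.0256/50) = 0.023 with 50.
- The bound varies more than the point estimate, because its standard error and degrees of freedom also rest on a variance estimated from only 5 values.
- At zero true difference the upper bound is expected near 1.96 × 0.36 ≈ 0.70. Its own sampling SE is about 0.36, so bounds close to 1 are not unusual.

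**HDP by hand, 40 observed per arm.** The SE is √(0.1667 × 0.8333 / 40) = 0.059. The expected lower bound is 0.1667 − 1.96 × 0.059 ≈ 0.05, about 5 percentage points above the threshold.

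**Simulation.** The same inputs were used with a true NRS difference of 0. Imputation was within arm (Bayesian normal for NRS, beta-binomial for HDP), pooled by Rubin's rules with the classical degrees of freedom. Outcomes were missing completely at random and equally by arm. Each simulated trial was imputed repeatedly under different seeds. Disagreement is the chance that two seeds give opposite verdicts on the same data.

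| Missing | Imputations | NRS bound SD (points) | NRS disagreement | HDP bound SD (percentage points) | HDP disagreement |
|---|---|---|---|---|---|
| 20% | 5 | 0.107 | 9.4% | 1.1–1.6 | 3–12% |
| 20% | 50 | 0.028 | 2–3% | 0.3–0.4 | 0–2% |
| 10% | 5 | 0.060 | 5.4% | 0.6–0.7 | 1.2–2.1% |
| 5% | 5 | 0.033 | 2.0% | 0.3–0.4 | 0.2–0.9% |

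The HDP ranges cover different imputation priors. With no events expected in the 2 mL arm, the prior carries real weight there. With 100 imputations at 20% missing, the NRS bound SD is 0.020 and disagreement 2.2%. If predictors explained an assumed 30% of NRS variance, 5 imputations would still give a bound SD of 0.084 and 8.3% disagreement.

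**The case against.** The strongest reply is that 20% is not a forecast of imputed outcomes, and this largely stands. The envelope is opened just before the block, and Definition of analysis populations limits the ITT set to patients who received the injection, so losses before the block would not be imputed under that definition. NRS is taken at first full consciousness. PACU discharge requires the diaphragm assessment to be complete. What remains is loss within a few hours under direct care. Final sample size determination also seems to treat dropouts as outside the ITT set and says that they will be replaced. Handling of study withdrawals says the opposite on replacement and keeps every randomized patient in the analysis. The amount to be imputed is therefore unsettled, and 20% is best read as a ceiling.

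Two further replies also stand in part. The pre-set seed rules out choosing among seeds. The complete-case re-analysis has no seed and would show up a seed-driven result. Neither removes the error from the primary analysis, which is the one that decides.

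A reader might also infer that the plan imputes HDP as a rare yes/no outcome from too many predictors. The article does not say so. It speaks of primary outcome data, names no imputation model and gives a predictor list that need not be complete. Imputing the excursion itself is not excluded, and the choice of model is ordinary content for the analysis plan, which is not shown.

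**Conclusion.** The point holds as a modest, specific improvement. Five imputations are too few for bounds that decide the trial if missingness comes anywhere near the level the trial is sized for. At that ceiling, the choice of seed alone moves the NRS upper bound by about ±0.21 points (1.96 × 0.107) against a 1-point margin. Fifty imputations cut this to about ±0.06 (1.96 × 0.028).

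It would be tempting to conclude that the trial's verdict will hang on the seed. The documents do not support that. At about 5% missing, seeds disagree in about 2% of pairs for NRS and under 1% for HDP, and collecting outcomes in the PACU makes low missingness plausible.

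The figures assume data missing completely at random, equal loss by arm, within-arm imputation and predictors explaining 0 to 30% of NRS variance. None of these is stated in the article. The HDP figures also depend on the prior.

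**What to change.** In Handling of missing data, replace the 5 imputations with at least 50 (100 is equally easy) and keep the fixed seed. This needs no patients, procedures or change to the total of 100, only minutes of computing, and can be done before database lock.

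Optionally, name baseline diaphragmatic excursion as an imputation predictor for HDP. It is already measured in every patient, and HDP is defined as a fall from it. Going further and deriving HDP from an imputed excursion would first need a convention for paradoxical movement and one reconciled HDP definition: the postoperative measurement section uses a single threshold of a 75% fall or more, while Primary outcomes lists complete and partial paresis. Raising the number of imputations does not depend on either.

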##### Analysis of primary outcomes

(1) Non-inferiority analysis of analgesic efficacy (pre-rescue NRS pain score)

The primary non-inferiority endpoint is the difference in pre-rescue NRS pain scores between the 2 mL group and the 5 mL group immediately after full consciousness in the PACU. The mean difference (MD) and its one-sided 97.5% confidence interval (CI) will be calculated using the two-sample t-test for independent samples, assuming equal variances.

*Non-inferiority judgment criterion*: The 2 mL regimen will be considered non-inferior to the 5 mL regimen in terms of analgesic efficacy if the upper bound of the one-sided 97.5% CI for the mean difference (2 mL group minus 5 mL group) is less than the predefined non-inferiority margin of 1 point.

(2) Superiority analysis of diaphragmatic safety (HDP incidence)

The primary superiority endpoint is the difference in the incidence of ipsilateral HDP between the two groups. The risk difference (RD) and its one-sided 97.5% CI will be calculated using the two-sample Z-test for proportions.

*Superiority judgment criterion*: The 2 mL regimen will be considered superior to the 5 mL regimen in terms of diaphragmatic safety if the lower bound of the one-sided 97.5% CI for the risk difference (5 mL group minus 2 mL group) is greater than 0.

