##### Sample size calculation based on HDP incidence superiority endpoint

The primary superiority endpoint is the difference in the incidence of ipsilateral HDP between the two groups. Based on the study by Zhang et al. (27), the incidence of HDP in patients receiving 5 mL 0.375% ropivacaine via subparaneural injection at the upper trunk bifurcation is 16.67%. Our preliminary study (n = 11) showed that no HDP occurred in patients receiving 2 mL 0.375% ropivacaine via the same technique, leading to our core hypothesis that the HDP incidence of the 2 mL regimen is infinitely close to 0.

However, the PASS 15.0.5 software does not allow setting the group proportion to 0 in the two-sample Z-test for superiority of proportions. To accurately reflect our preliminary findings and satisfy the software’s calculation requirements, we set the HDP incidence in the 2 mL group to an extremely small value of 1 × 10^−20^, which is mathematically indistinguishable from 0 for all practical clinical purposes.

Using the two-sample Z-test for superiority of proportions with pooled variance, the required sample size per group is calculated as follows:
$$n=\frac{{\left(Z_{1-\alpha }+Z_{1-\beta }\right)}^{2}(p_{1}(1-p_{1})+p_{2}(1-p_{2}))}{{\left(p_{1}-p_{2}\right)}^{2}}$$
Where 
$p_{1}=0.166667$
 (HDP incidence in the 5 mL group), 
$p_{2}=1\times 10^{-20}$
 (estimated HDP incidence in the 2 mL group), 
$Z_{1-\alpha }=1.96$
, and 
$Z_{1-\beta }=0.84$
. Substituting the values yields a required sample size of 40 patients per group.

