##### Analysis of secondary outcomes

*Continuous variables*: Normally distributed data (e.g., diaphragmatic excursion, FEV1, FVC, emergence time, PACU stay duration) will be presented as mean ± standard deviation (SD), and between-group differences will be analyzed using the two-sample t-test. Non-normally distributed data (e.g., analgesic drug consumption, postoperative hospital length of stay) will be presented as median (interquartile range, IQR), and between-group differences will be analyzed using the Mann–Whitney U test.*Categorical variables*: Data will be presented as counts (percentages). Between-group comparisons will be performed using the chi-square (χ^2^) test for large sample sizes or Fisher’s exact test for cell counts < 5.*Ordinal variables* (e.g., sensory and motor block scores): Between-group differences will be analyzed using the Mann–Whitney U test.

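### The primary HDP analysis is a large-sample Z interval in a trial planned for about zero events in one arm: it declares superiority at 4 vs 0, where exact tests do not, and modestly exceeds its 2.5% level over part of the range

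*Protocol article*

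**What the plan says.** Under Analysis of primary outcomes, the HDP endpoint is analysed as follows: "The risk difference (RD) and its one-sided 97.5% CI will be calculated using the two-sample Z-test for proportions". The 2 mL regimen is superior "if the lower bound of the one-sided 97.5% CI for the risk difference (5 mL group minus 2 mL group) is greater than 0". No continuity correction, score method or exact method is named.

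The Sample size calculation works "with a one-sided significance level (*α*) of 0.025 and a statistical power (1-*β*) of 0.80". Its HDP subsection takes 16.67% for the 5 mL arm from a published study. For the 2 mL arm it states a "core hypothesis that the HDP incidence of the 2 mL regimen is infinitely close to 0" and enters that as follows: "we set the HDP incidence in the 2 mL group to an extremely small value of 1 × 10^−20". That subsection calls the variance pooled, but the formula it prints is unpooled. The result is 40 per group, raised to 50 for 20% dropout.

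Fisher's exact test for HDP appears only under Sensitivity analyses. For secondary categorical outcomes the plan uses Fisher's "exact test for cell counts < 5". Under Multiplicity adjustment, both co-primary endpoints must succeed. Missing primary outcomes are multiply imputed, and SPSS is the named software.

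**The concern.** A Z interval for a risk difference relies on a normal approximation in each arm, and the plan expects one arm to have no events, where that approximation is weakest. With the unpooled variance, an arm with 0 events contributes nothing to the standard error, so its rate is treated as known. Yet 0/50 is compatible with a true rate of up to 7.1% (exact one-sided 97.5% bound), and 0/40 with up to 8.8%.

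Two things are at stake. First, the one-sided 2.5% level may not hold. Second, the trial could claim diaphragmatic safety on 4 or 5 events against none while its own sensitivity test is not significant. The plan gives no rule for that case. Because HDP is co-primary, overall success depends on this rule.

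**Working it through.** **Inputs.** One-sided α 0.025 and power 0.80 (Sample size calculation); 16.67% vs 10⁻²⁰ (HDP subsection); 40 evaluable and 50 recruited per arm (Final sample size determination); the Z rule (Analysis of primary outcomes). Expected events in the 5 mL arm: 40 × 1/6 = 6.7 and 50 × 1/6 = 8.3.

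**The plan's own figure.** n = (1.96 + 0.84)² × [p₁(1 − p₁) + p₂(1 − p₂)] / (p₁ − p₂)² = 7.84 × 0.1389 / 0.02778 = 39.2, rounded up to 40. It reproduces with the printed unpooled formula. A truly pooled calculation gives 42.

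**Smallest success against 0 events.** Let a be the events in the 5 mL arm.

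- Unpooled lower bound: a/n − 1.96 × √[(a/n)(1 − a/n)/n].
  - n = 50, a = 4: 0.08 − 1.96 × √(0.08 × 0.92/50) = 0.08 − 0.0752 = +0.0048.
  - n = 40, a = 4: 0.10 − 1.96 × √(0.10 × 0.90/40) = 0.10 − 0.0930 = +0.0070.
  - a = 3: −0.0058 (n = 50) and −0.0066 (n = 40), so no success.
- Pooled z, a = 4: 0.08/√(2 × 0.04 × 0.96/50) = 2.041 (p = 0.0206); for n = 40, 2.052 (p = 0.0201). Both exceed 1.96.
- One-sided Fisher, 4 vs 0: C(50,4)/C(100,4) = 0.0587; C(40,4)/C(80,4) = 0.0578.
- One-sided Boschloo, 4 vs 0: 0.0443 (n = 50) and 0.0410 (n = 40).
- 5 vs 0: Fisher 0.0281 and 0.0274; Boschloo 0.0176 and 0.0165.

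At both sample sizes the Z rule therefore needs 4 vs 0, Boschloo 5 vs 0 and Fisher 6 vs 0.

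**Actual one-sided size.** Both binomials were enumerated in full at a common true rate.

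| Rule | n per arm | Maximum size | Size at 8.33% | Size at 16.67% |
|---|---|---|---|---|
| Z, unpooled | 50 | 3.07% (at 7.6%) | 3.06% | 2.85% |
| Z, unpooled | 40 | 2.95% (at 9.2%) | 2.93% | 2.62% |
| Z, pooled | 50 | 2.84% (at 50%); 2.75% for rates up to 30% | 2.38% | 2.72% |
| Z, pooled | 40 | 2.95% (at 9.2%) | 2.93% | 2.62% |
| Fisher | 50 | 1.76% | 0.76% | 1.28% |
| Fisher | 40 | 1.65% | 0.63% | 1.34% |

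The unpooled rule exceeds 2.5% from a common rate of about 4.6% (50 per arm) or 5.9% (40 per arm). Below that it is conservative: 0.66% at a 2% rate with 50 per arm.

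**Power at 16.67% vs 0%**, that is P(X ≥ critical count) with X ~ Bin(n, 1/6):

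| Rule (critical count) | 40 per arm | 50 per arm |
|---|---|---|
| Z (4) | 91.9% | 97.6% |
| Boschloo (5) | 81.9% | 93.6% |
| Fisher (6) | 67.6% | 86.1% |

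**Disagreement between the Z rule and Fisher**, P(X = 4 or 5): 4.0% + 7.5% = 11.5% at 50 per arm; 9.9% + 14.3% = 24.3% at 40 per arm (unrounded components).

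**The case against.** The protocol does not name the unpooled (Wald) interval. The one place that names a variance type says pooled, and under that reading the size at 50 per arm is below 2.5% near an 8% common rate. This stands: the 3.07% figure and the vanishing variance belong to the unpooled reading. The reading does not affect the 4 vs 0 result, and both readings exceed 2.5% somewhere.

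The excess is also small, at most about 0.6 percentage points. Because success needs the NRS endpoint too, false overall success is lower still. With non-inferiority power of about 0.87 at 50 per arm (SD 1.6, no true difference) and independent endpoints, it is 0.0307 × 0.87 = 2.7%. This stands as well.

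Fisher's test is already planned, so a fragile result would be visible. But it has no stated consequence. Fisher is itself conservative, so its disagreement alone does not prove the primary test wrong. The stronger evidence is that the exact unconditional test also stays above 0.025 at 4 vs 0.

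A reader might infer that the plan contradicts itself by requiring an exact test for sparse tables. It does not: that rule covers secondary outcomes only, and the contrast is merely telling. Nor does the point show that the sample size is miscalculated, since 40 per group reproduces.

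Finally, near-zero events is the plan's own assumption. The outcome definition also lists partial paresis (25–75% reduction); if that counts as HDP, an empty 2 mL arm is less assured.

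**Conclusion.** The concern holds in a limited form. The stated primary rule declares superiority at 4 vs 0 under either variance reading and at either sample size, where one-sided exact p-values are 0.041 to 0.059 against a level of 0.025. The level is exceeded modestly and only over part of the range: up to 3.07% (unpooled) or 2.84% (pooled) at 50 per arm, and 2.95% under both readings at 40. The rule is conservative when both true rates are below about 5%.

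A reader might go further and conclude that the error rate is generally or seriously inflated. The figures do not support that. The practical weight lies in the fragile success at 4 or 5 vs 0 and in the foreseeable split from the plan's own sensitivity test (11.5% or 24.3% of trials).

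These figures assume complete HDP data, equal arms of 40 or 50, no continuity correction and, for power and disagreement, true rates of 16.67% and 0%. The change is worth making, but the flaw does not invalidate the design.

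**What to change.** Before database lock, make a one-sided 0.025 exact unconditional test (Boschloo) the primary HDP analysis, with a matching test-inversion interval for the risk difference. Keep Fisher's test as a sensitivity analysis and report the exact upper bound for the 2 mL rate. No extra patients are needed: the stated 80% power for this endpoint is kept at both sample sizes.

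Three costs should be stated:

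- **Software.** The test and interval need software beyond the named SPSS. R is already used for the randomisation list.
- **Missing data.** The plan imputes missing primary outcomes, and exact p-values have no routine pooling rule. One option is the exact test on observed HDP outcomes, with the multiply imputed analysis as sensitivity. Another is a Newcombe/Wilson-type interval for the imputed analysis. It also needs 5 vs 0, and its size is about 2.5% at most for common rates up to 30%.
- **Remaining disagreement.** Boschloo and Fisher still split at 5 vs 0, in 7.5% of trials at 50 per arm and 14.3% at 40. The plan should say in advance that the primary test decides.

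If the Z-test is kept instead, the protocol should at least name the variance and say how a conflict with Fisher's test will be interpreted.

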##### Analysis of secondary outcomes

*Continuous variables*: Normally distributed data (e.g., diaphragmatic excursion, FEV1, FVC, emergence time, PACU stay duration) will be presented as mean ± standard deviation (SD), and between-group differences will be analyzed using the two-sample t-test. Non-normally distributed data (e.g., analgesic drug consumption, postoperative hospital length of stay) will be presented as median (interquartile range, IQR), and between-group differences will be analyzed using the Mann–Whitney U test.*Categorical variables*: Data will be presented as counts (percentages). Between-group comparisons will be performed using the chi-square (χ^2^) test for large sample sizes or Fisher’s exact test for cell counts < 5.*Ordinal variables* (e.g., sensory and motor block scores): Between-group differences will be analyzed using the Mann–Whitney U test.

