### Baseline pulmonary function test and diaphragmatic excursion measurement

Subjects sign the written informed consent form one day before surgery, and remain fully blinded to their group allocation throughout the perioperative period. No premedication is administered to any subject in the ward before surgery.

On the day of elective surgery, all subjects follow the standard preoperative fasting protocol, with 8 h of fasting for solid food and 2 h of fasting for clear liquids. After entering the operating room, a peripheral venous access is established on the non-operative upper limb of each subject, followed by a rapid infusion of 8 mL/kg lactated Ringer’s solution over 15–20 min for initial volume expansion. For patients with a history of cardiovascular disease (including heart failure, coronary artery disease, or hypertension), the infusion rate and total volume will be individually adjusted based on clinical assessment to avoid volume overload. Standard non-invasive monitoring is initiated immediately, including continuous electrocardiogram (ECG), non-invasive blood pressure (NIBP), and pulse oxygen saturation (SpO₂). Baseline vital signs (heart rate, systolic blood pressure, diastolic blood pressure, mean arterial pressure, and SpO₂) are recorded before any anesthetic or study intervention, and all intraoperative vital signs are continuously documented in the electronic anesthesia record system throughout the procedure.

Immediately after the above preoperative preparation is completed and strictly before the implementation of the study intervention (ultrasound-guided subparaneural block at the brachial plexus upper trunk bifurcation), all baseline diaphragmatic excursion and pulmonary function measurements are performed. The core purpose of these measurements is to obtain paired baseline data for the primary and secondary endpoints of this patient- and outcome assessor-blinded randomized controlled trial, so as to evaluate the differences in diaphragmatic function and pulmonary function between the 2 mL and 5 mL 0.375% ropivacaine groups after the study intervention.

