#### Postoperative pulmonary function test and diaphragmatic excursion measurement

All postoperative pulmonary function and diaphragmatic excursion measurements are independently completed by [name], the same investigator who performed the preoperative baseline assessments, to eliminate inter-operator variability and ensure the consistency and comparability of paired pre- and post-intervention data.

The measurements are performed when the subject is fully awake, has stable spontaneous breathing, and can accurately follow standardized verbal instructions, strictly before discharge from the PACU. The subject’s body position, equipment used, operational procedures, quality control standards, and data calculation methods for the measurements are completely consistent with those used for the preoperative baseline assessments.

Hemidiaphragmatic paralysis (HDP) is defined as a decrease in postoperative diaphragmatic excursion of ≥75% compared with the baseline value, or the presence of paradoxical diaphragmatic movement during breathing. The incidence of HDP is recorded as one of the co-primary endpoints of the trial. The absolute and percentage changes in diaphragmatic excursion, forced expiratory volume in 1 s (FEV1), and forced vital capacity (FVC) from baseline to postoperative measurement are calculated for each subject as key secondary endpoints of the trial.

All postoperative measurement data are entered into a standardized CRF marked only with the subject’s unique study ID in real time, and independently double-entered into the study-specific locked electronic database by two other researchers not involved in the measurement or intervention procedures, with cross-verification performed to ensure the integrity, accuracy and traceability of the paired data.

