##### Multiplicity adjustment

No multiplicity adjustment will be performed for the two co-primary endpoints, as they address distinct and independent research questions (analgesic efficacy vs. diaphragmatic safety), and both must be statistically significant to declare the overall success of the trial.All secondary outcomes are exploratory in nature and will not undergo multiplicity adjustment. Results will be presented with point estimates and 95% CIs, and *p* values will be interpreted descriptively rather than as definitive hypothesis tests.

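### Excursion, FEV1 and FVC are compared without adjustment for their paired baselines: an avoidable loss of precision on exploratory outcomes, not a bias

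*Protocol article*

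**What the plan says.** In the protocol article, *Analysis of secondary outcomes*, the rule for continuous data opens with "Normally distributed data (e.g., diaphragmatic excursion, FEV1, FVC, emergence time, PACU stay duration" and then states that "between-group differences will be analyzed using the two-sample t-test". Continuous data that are not normal go to the Mann–Whitney U test. No covariate-adjusted model appears anywhere under *Statistical analysis*.

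*Secondary outcomes* lists three quantities for each measure: the value before PACU discharge, the absolute change from baseline and the percentage change from baseline.

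The baseline is collected with care. *Baseline pulmonary function test and diaphragmatic excursion measurement* states: "The core purpose of these measurements is to obtain paired baseline data for the primary and secondary endpoints". The postoperative measurement section uses the same assessor throughout, in order to "ensure the consistency and comparability of paired pre- and post-intervention data". It also describes the absolute and percentage changes as key secondary endpoints.

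*Multiplicity adjustment* sets the inferential status: "All secondary outcomes are exploratory in nature and will not undergo multiplicity adjustment". On reporting it says "Results will be presented with point estimates and 95% CIs", with p values read descriptively.

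**The concern.** The trial standardises position, equipment, method and assessor so that each patient's PACU reading can be set against that patient's own baseline. The analysis then makes little use of the pairing. A t-test on the PACU value ignores the baseline. A t-test on absolute change subtracts all of it, which is too much whenever the regression slope of the PACU value on baseline is below 1.

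These measures matter for interpretation. The sample size section assumes HDP in 16.67% of the 5 mL arm and essentially none of the 2 mL arm, or about 50 × 0.1667 ≈ 8 events against 0. Excursion and spirometry are therefore the main graded evidence on diaphragm sparing, and they will be read through their confidence intervals. Wider intervals than necessary make that evidence less informative.

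**Working it through.** **The plan's own figures.** The article gives no sample size, power or precision figure for these secondary outcomes. Its sizing uses a "one-sided significance level (*α*) of 0.025 and a statistical power (1-*β*) of 0.80" for the co-primaries only:

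- NRS: 2 × (1.96 + 0.84)² × 1.6² / 1² = 40.14, against the stated 40.
- HDP: (1.96 + 0.84)² × (0.1667 × 0.8333) / 0.1667² = 39.2, so 40.
- Dropout: 40 / (1 − 0.20) = 50 per group.

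None of this depends on how excursion, FEV1 or FVC are analysed.

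**Inputs for the comparison.**

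- 50 per arm, 1:1 (*Final sample size determination*).
- r, the within-arm correlation of baseline and PACU value: not in the article; assumed 0.3 to 0.9.
- Equal SDs at baseline and in the PACU: assumed.

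**Formulas.** Each analysis in effect compares arms on Y − bX, where Y is the PACU value and X the baseline. The variance per patient is σ_Y² + b²σ_X² − 2b·r·σ_X·σ_Y. With both SDs set to 1:

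- PACU value only (b = 0): 1
- absolute change (b = 1): 2(1 − r)
- ANCOVA (b = r, the minimising value): 1 − r²

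So ANCOVA / PACU value = 1 − r², and ANCOVA / change = (1 − r²) / [2(1 − r)] = (1 + r)/2. The CI width ratio is the square root of the variance ratio. The number of patients that the planned test would need to match 100 under ANCOVA is 100 divided by the variance ratio.

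| r | Variance vs PACU value | Variance vs change | CI width vs PACU value | CI width vs change | 100 under ANCOVA equals (PACU value / change) |
|---|---|---|---|---|---|
| 0.3 | 0.91 | 0.65 | 0.95 | 0.81 | 110 / 154 |
| 0.5 | 0.75 | 0.75 | 0.87 | 0.87 | 133 / 133 |
| 0.7 | 0.51 | 0.85 | 0.71 | 0.92 | 196 / 118 |
| 0.9 | 0.19 | 0.95 | 0.44 | 0.97 | 526 / 105 |

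**Simulation at 50 per arm** (4,000 replicates; variance of the estimated difference as a multiple of 2/n):

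| r | PACU value | Change | ANCOVA |
|---|---|---|---|
| 0.3 | 0.98 | 1.37 | 0.90 |
| 0.5 | 0.97 | 0.98 | 0.73 |
| 0.7 | 1.01 | 0.60 | 0.51 |
| 0.9 | 1.00 | 0.20 | 0.20 |

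These agree with the formulas.

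**Chance imbalance.** The SE of the difference in baseline means is √(2/50) = 0.2 SD, so an imbalance beyond 0.2 SD in either direction has about a 32% chance for each measure. Given an imbalance d, the PACU-value comparison shifts by r·d and the change comparison by (1 − r)·d in the opposite direction. Two of the listed quantities can therefore point different ways in the same dataset. ANCOVA corrects for d. The shifts average to zero over randomizations and are already inside the t-test standard errors, so they are the source of the extra variance and not a separate defect.

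**The case against.** Several stronger readings are tempting, and the document does not support them.

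*That the planned comparisons are biased or invalid.* They are not. Under 1:1 randomization, t-tests on the PACU value and on absolute change are unbiased and their intervals are valid.

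*That the baseline is thrown away.* It is not. Absolute and percentage change are listed outcomes, and the postoperative measurement section makes those changes, not the raw PACU values, the key secondary endpoints. The full loss from ignoring baseline falls only on the raw-value comparison.

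*That all three quantities are forced into t-tests, including a skewed percentage change.* The normality condition sends non-normal data to Mann–Whitney, and the named variables are examples. Nothing in the article suggests that baselines are small enough to make percentages unstable.

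*That the gain is always large.* Repeated measurement by one assessor with one method, averaging three readings, may produce a high r. At r = 0.9 ANCOVA improves on the change score by only 5% in variance. Paresis in a minority of one arm could also break the equal-SD assumption.

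*That a trial conclusion is at risk.* The secondaries are exploratory, and success and sample size rest on the co-primaries alone.

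All of this stands as a limit on severity. It does not remove the point. The article itself fixes the test for these named variables, so this is not a detail left to an unseen SAP. The exploratory label is no defence either, because the outcomes will be reported as estimates with 95% CIs, and interval width is what baseline adjustment improves.

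**Conclusion.** The point holds as a minor improvement in efficiency. The planned tests for excursion, FEV1 and FVC are valid but less precise than an analysis that the collected data already allow.

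Assuming r between 0.3 and 0.9 and equal SDs, ANCOVA cuts variance by 9% to 81% relative to the PACU-value t-test and by 35% to 5% relative to the absolute-change t-test. At r = 0.5 the cut is 25% against either, with intervals about 13% narrower. The two gains move in opposite directions as r rises, so neither planned test is safe across the range. ANCOVA is the more precise of the three for any r strictly between 0 and 1, so r need not be known in order to prefer it.

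The exact ratios rest on the equal-SD assumption. The ordering needs only large samples and 1:1 allocation, because ANCOVA uses the minimising b. The ratios do not carry over exactly to percentage change. The co-primary analyses and N = 100 are untouched.

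**What to change.** In *Analysis of secondary outcomes* and in the SAP, state that the main between-group estimate for each of excursion, FEV1 and FVC is an ANCOVA of the PACU value on arm plus that measure's own baseline, reported as an adjusted mean difference with 95% CI. This also settles which of the three listed quantities carries the main comparison.

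Keep the absolute and percentage changes as supportive summaries. Percentage change in excursion should stay visible, because a percentage fall in excursion is the scale on which HDP is defined. A reader might think that moving to ANCOVA means dropping it; that is unnecessary and would separate the continuous result from the co-primary that it helps to explain.

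The cost is a few lines of text. The baselines are already collected, the model is standard in the named software (SPSS), and no patients or visits are added. The article finalises the SAP before database lock and places lock in January to February 2027, so the change can still be pre-specified.
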